### Intervention

#### Group-based SE® Intervention.

Participants in the intervention arm will attend 10 weekly group sessions (3 hours/session) of manualized, group-based SE® intervention based on SE® principles. The intervention emphasizes bottom-up processing of trauma, stabilization of the autonomic nervous system, and completion of incomplete defensive responses. A Module Structure of Group-based SE® sessions is presented in Table 1.

**Table 1 pone.0336956.t001:** Module Structure of Group-based SE® sessions.

No	Module Title	Content/Activities	Intention	Target Issues	Skill Taught	Homework	Supplies
1	Preparatory 1	• Welcome and Introduction • Facilitator greeting, acknowledging courage to attend • Icebreaker: each participant states their name and one personal resource • Building cohesion and safety • Orientation exercise • Group agreement: • Psycho- education: Introduce SE**®** and PTSD • Brief explanation of trauma as incomplete defensive responses • Importance of body-based approaches and group support. • How SE**®** group can help • Experiential Exercise: • Guided practice • Invite sharing • Normalize varied responses • Integration and Group Agenda • Reflection • Collect and record group goals • Emphasize collaborative ownership process • Closing •Summarize today’s agenda • Introduce homework • Closing ritual: each participant shares one word/gesture for how they leave the session	• Build group cohesion and establish a sense of safety. • Orient participants to group purpose, structure and rules. • Introduce SE® and its relevance to PTSD recovery • Facilitate gentle re-connection to bodily sensation and resources	• Relational safety and trust. • Disconnection from the body and avoidance of interoception • Uncertainty about group role, expectations, and confidentiality • Normalization and universality (reducing isolation).	• Grounding and orienting in the present moment. • Identifying and using internal and external resources. • Sensation tracking (pleasant, neutral, unpleasant). • Respectful communication and group process skills.		• Name cards • Sensation name cards • SE®PowerPoint

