### Treatment As Usual (TAU)

Participants in the control arm will receive five group counselling sessions (90minutes per session) over five weeks. These sessions focus on psychoeducational counseling session, covering basic mental health support strategies and coping techniques, and are facilitated by licensed psychologist. The decision to provide five 90 minute per sessions is based on evidence from Indonesian research and practice, which showing that survivors of sexual assault typically receive between 4–7 session of psychological support(Ayudia et al. 2025c; Sumekar and Sunawan 2019).

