### Sample size

A priori power analysis using G*Power 3.1 estimated a required total sample size of 207 participants (138 intervention, 69 control) to detect a medium effect size (Cohen’s d = 0.5), with α = 0.05, power = 0.80, and accounting for 30% attrition.

The choice of medium effect size (d = 0.5) is based on prior meta-analytical findings from studies evaluating SE® and other body-oriented trauma interventions among individual PTSD or complex trauma symptoms. Specifically, Payne et al [7] and Andersen et al [16–18] report medium to large effect sizes in PTSD symptom reduction following SE® informed interventions. Given the cultural adaptation and group-based format in this study, a conservative medium effect size was deemed appropriate.

Participants will be randomized in a 2:1 allocation ratio using block randomization generated through Castor EDC software.

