### Statistical analysis plan

All statistical analyses will be performed using SPSS version 22.0.

Descriptive statistics will be used to summarize demographic and clinical characteristics of the participants.Baseline differences between groups will be examined using chi-square test for categorical variables and t-test for continuous variables.To evaluate treatment effects, linear mixed-effect models will be used to analyse the interaction of time (T0, T1, T2, T3) and group condition (intervention vs control) on primary and secondary outcomes.The models will include fixed effects for time, group, and time x group interaction, and random intercepts for participants to account for within subject variability across time points.To minimize confounding related to unequal treatment exposure, total professional contact time (minutes) within and outside the study will be logged for each participant. In prespecified secondary analyses, this variable will be included as a covariate in the mixed-effects models. Additional sensitivity analyses will be conducted, including (i) exclusion of participants who receive substantial trauma-focused services outside the protocol, (ii) per-protocol analyses restricted to participants with adequate adherence (≥ 80% of assigned sessions), and (iii) exploratory dose-response models testing the interactions between group assignment and contact time. These steps will allow us to assess whether intervention effects remain robust after adjusting for variation in professional contact time.Effect sizes will be reported using Cohen’s d.All analyses will follow the intention-to-treat (ITT) principle, including all randomized participants. Missing data will be handled using regression imputation under the assumption that data are missing at random (MAR). Specifically, predictive mean matching will be used to impute missing continuous outcome variables, which is considered appropriate for longitudinal clinical trial data.

To control for the increased risk of Type I error due to multiple comparisons across outcomes, A Bonferroni correction will be applied.

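### Both arms are treated in therapy groups, but the mixed model and the sample size treat participants as independent, so standard errors are too small if outcomes correlate within groups, and 80% power is not assured

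*Protocol article*

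**What the plan says.** The unit of randomisation is the woman: "Participants will be randomized in a 2:1 allocation ratio using block randomization" (Sample size). Treatment is then given in groups in both arms. For Somatic Experiencing (SE), "Participants in the intervention arm will attend 10 weekly group sessions (3 hours/session"; for treatment as usual (TAU), "Participants in the control arm will receive five group counselling sessions".

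The Statistical analysis plan section specifies a linear mixed model with fixed effects for time, group and their interaction. Group there means trial arm. The only random effect is "random intercepts for participants to account for within subject variability across time points". The listed secondary and sensitivity analyses cover contact time, outside services, adherence and dose-response. None concerns the therapy group or the facilitator.

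The Sample size section reports that "A priori power analysis using G*Power 3.1 estimated a required total sample size of 207 participants", split as "138 intervention, 69 control", "to detect a medium effect size (Cohen’s d = 0.5"), "with α = 0.05, power = 0.80, and accounting for 30% attrition". No group size, intraclass correlation (ICC) or design effect appears.

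**The concern.** Women in one therapy group share facilitators, sessions and each other. The Introduction counts co-regulation and peer support among the advantages of the group format, and Table 1 makes cohesion an aim of the sessions. Assuming no correlation within groups sits badly with that rationale.

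A therapy-group effect starts after T0 and is common to several women. A participant intercept is constant over time and specific to one woman, so it cannot represent such an effect. The time-by-arm test then counts correlated women as independent: standard errors are too small, confidence intervals too narrow, and a false-positive finding on PCL-5 more likely than the nominal level says. A power statement without a design effect has the matching weakness.

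**Working it through.** **1. Reproducing 207.** Inputs from the Sample size section: d = 0.5, α = 0.05 (two-sided, which is what reproduces the figure), power 0.80, 2:1 allocation, 30% attrition. A two-sample t-test with 96 + 48 = 144 analysed has power 0.802. Per arm, 96/0.7 = 137.1, rounded up to 138, and 48/0.7 = 68.6, rounded up to 69; the total is 207. The match is exact, so the design effect used was 1, and there is almost no slack.

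**2. Assumptions, because the document is silent.** Groups of m = 8 or 10; ICC 0.02, 0.05 or 0.10.

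**3. Power on the protocol's own two-sample basis.** Evaluable numbers: 138 × 0.7 = 96.6 and 69 × 0.7 = 48.3. Groups shrink to 0.7m, so the design effect is DE = 1 + (0.7m − 1) × ICC. The noncentrality is 0.5 × √[96.6 × 48.3 / (144.9 × DE)] = 2.837/√DE. Degrees of freedom are the number of groups minus 2: about 26 − 2 = 24 for m = 8, and about 21 − 2 = 19 for m = 10.

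| ICC | DE, m = 8 | Power, m = 8 | DE, m = 10 | Power, m = 10 |
|---|---|---|---|---|
| 0 | 1.00 | 78% | 1.00 | 77% |
| 0.02 | 1.09 | 74% | 1.12 | 72% |
| 0.05 | 1.23 | 69% | 1.30 | 66% |
| 0.10 | 1.46 | 62% | 1.60 | 57% |

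The ICC = 0 row shows that 2 to 3 points of the drop come from degrees of freedom alone.

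**4. Power if baseline is used.** Replace DE by V = (1 − r²)(1 − ICC) + 0.7m × ICC, where r is the assumed baseline correlation and the therapy-group variance is not reduced by baseline. For r = 0.5 to 0.7:

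| ICC | m = 8 | m = 10 |
|---|---|---|
| 0.02 | 84–94% | 82–92% |
| 0.05 | 78–88% | 74–84% |
| 0.10 | 69–77% | 63–71% |

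**5. Type I error of the planned model, Week-10 contrast.** The planned random-intercept test was simulated with 138/69 complete data, within-person correlation 0.5 and a therapy-group effect added at T1–T3. Without clustering it holds 5%. With groups of 8 to 10 it rejects in about 7–8%, 9–10% and 15% of null trials at ICC 0.02, 0.05 and 0.10.

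A closed form agrees. Let a woman's outcome variance be 1 without the therapy-group effect, and let the therapy-group variance be v = ICC/(1 − ICC). The true variance of a change from T0 to T1, averaged over n women, is (1 + m·v)/n. The model's within-person residual picks up only a quarter of v, so it uses (1 + 0.5v)/n. The actual level is 2[1 − Φ(1.96/√R)] with R = (1 + m·v)/(1 + 0.5v).

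| ICC | v | R, m = 8 | Level | R, m = 10 | Level |
|---|---|---|---|---|---|
| 0.02 | 0.0204 | 1.15 | 6.8% | 1.19 | 7.3% |
| 0.05 | 0.0526 | 1.38 | 9.6% | 1.49 | 10.8% |
| 0.10 | 0.1111 | 1.79 | 14.3% | 2.00 | 16.6% |

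At within-person correlation 0.7 the leading 1 in both parts of R becomes 0.6, which makes matters worse. For m = 8 and ICC 0.05, R = 1.021/0.626 = 1.63 and the level is about 12.5%.

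**The case against.** **Power.** A reader might infer that the trial certainly misses 80%. The document does not support that. The figures in step 3 rest on a post-treatment comparison that ignores T0, while the planned model uses T0 and repeated measures. Step 4 shows a properly clustered analysis above 80% throughout at ICC 0.02 and over part of the range at 0.05, though below it throughout at 0.10. This stands. However, the Sample size section claims no such gain, and a gain in power does not repair understated standard errors. The higher correlation that restores power also increases the type I inflation of the planned model.

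**Bonferroni.** A reader might also infer that the error rate exceeds 5% however the plan is read. It need not. The divisor is not stated, but if the correction spans three instruments the nominal level is 0.05/3 = 1.67%, and the simulated PCL-5 rejection rate at ICC 0.05 and correlation 0.5 is close to 5% or just under. It exceeds 5% at ICC 0.10. The correction is meant for multiple outcomes. It lowers the nominal level and leaves the standard errors wrong.

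**Different bases.** The type I figures use full groups and complete data, and the power figures use groups reduced by attrition. With attrition-sized groups (97/48 analysed, starting from groups of about 8), the error rate is lower: about 6.4%, 7.5% and 12% at the three ICCs.

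**Unknown ICC.** The co-regulation rationale supports a non-zero ICC, not any particular size. At ICC 0.01 the loss of power from correlation is only a few points.

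**Left to a fuller plan.** The article itself fixes the random-effects structure and the power inputs, so this is a stated choice and not an omitted detail.

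**Conclusion.** The point holds in conditional form. It is certain from the text that both arms are group-treated, that the model has no therapy-group term, and that 207 assumes independent observations. If outcomes correlate within therapy groups, as the protocol's own rationale implies, the planned standard errors are too small.

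Under the stated assumptions the nominal 5% Week-10 test runs at about 7–8% to 15% over ICC 0.02 to 0.10. Power on the protocol's two-sample basis falls to between 74% and 57%. Whether the trial finally has 80% depends on group size, ICC and baseline correlation, none of which is given. The stated 80% is therefore not assured, which is weaker than saying it is missed. The correction should be made before recruitment, because therapy-group membership that was never recorded may be impossible to recover.

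**What to change.** - **Data.** Record the assigned therapy group for every participant in both arms. Keep the assigned group for analysis even if some sessions are attended with another group, which the flexible scheduling under Recruitment and setting makes possible.
- **Model.** Keep T0 in the analysis in one of two ways: add to the planned model a random therapy-group effect that acts only at T1–T3, or model T1–T3 with baseline PCL-5 as a covariate and a therapy-group random intercept. In both cases keep the participant effect and use Satterthwaite degrees of freedom. SPSS MIXED can fit this.
- **Variance by arm.** Let the therapy-group variance differ by arm if it can be estimated. The control arm would have only about 69/10 ≈ 7 to 69/8 ≈ 9 groups, so prespecify a common variance as the fallback.
- **Sample size section.** State the planned group size and restate the power of 207 as a range over ICC 0.02 to 0.10. State the assumed baseline correlation if one is used.

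The cost is one identifier field, one extra random effect, a less favourable stated power and slightly wider confidence intervals. No extra participants are needed.

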### Limitations

This study has several limitations. First, despite efforts to balance treatment exposure, a discrepancy in contact time remains between the SE® intervention (10 sessions x 180 minutes) and the TAU arm (5 sessions x 90 minutes). This discrepancy introducing bias. However, the design of TAU reflects the real-world availability of services in Indonesia, where survivors of sexual assault typically have limited and sporadic access to structured trauma-focused therapy. To address this issue, will be committed to controlling for total minutes of professional contact as a covariate in secondary analyses. Sensitivity analyses will also be conducted to test whether outcomes remain robust after adjusting for contact time.

Second, while the number of session differs between arms, it is important to emphasize that the aim of this trial is not to determine which treatment is superior, but rather to evaluates the effectiveness of culturally adapted SE® intervention relative to the benchmark of usual care in Indonesia. In this sense, TAU serves as a pragmatic comparator that mirrors local service provision, rather than a dose-matched control condition. This design enhances ecological validity and translational relevance, though it limits strict comparability of treatment ‘‘dose.’’

Third, TAU is based on psychoeducational counselling rather than trauma-specific intervention. While this may reduce comparability in therapeutic content, it pragmatically reflects current service delivery in Indonesia, thus increasing ecological validity and translational relevance.

Fourth, blinding of participants is not feasible due to the nature of the intervention, which may increase the risk of expectancy effects. Finally, the trial is conducted within one cultural and geographical setting, which may limit generalizability to other populations. Nonetheless, focus on cultural adaptation offers insight that could guide implementation in similar low-resource and collectivist context.

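### The contact-minutes covariate cannot test robustness to the contact-time imbalance: as written it leaves time x group unchanged, and forms that do act condition on a post-randomisation variable largely set by arm

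*Protocol article*

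**What the plan says.** The Limitations section of the protocol article gives the planned contact as "10 sessions x 180 minutes) and the TAU arm (5 sessions x 90 minutes" and accepts that the difference biases the comparison. Two remedies are offered there: contact minutes as a covariate in secondary analyses, and a further promise, "Sensitivity analyses will also be conducted to test whether outcomes remain robust after adjusting for contact time".

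The Statistical analysis plan section defines the model. It has fixed effects for time (T0 to T3), group and their interaction, with a random intercept per participant. The treatment effect is the time x group interaction. Minutes inside and outside the study are logged as one total per participant, and "In prespecified secondary analyses, this variable will be included as a covariate in the mixed-effects models". No product of contact with time is mentioned. The same paragraph adds "exploratory dose-response models testing the interactions between group assignment and contact time", again without a time term, and concludes that these steps will show whether the effect survives adjustment for contact. Missing continuous outcomes are to be imputed.

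**The concern.** A total that is constant within a participant carries only between-participant information, whereas the treatment effect in this model is a within-participant contrast compared between arms. The adjusted and unadjusted interactions will therefore agree whatever role contact plays. That agreement would be read as evidence that the effect does not depend on a four-fold difference in contact.

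If the covariate is instead given a form that can change the interaction, a second problem arises. Minutes are a consequence of assignment and attendance, so conditioning on them no longer compares the groups as randomised.

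At stake is the protocol's analytic answer to the first limitation it lists, and any published statement that the effect is robust to contact time.

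**Working it through.** **Inputs.** From Sample size: "estimated a required total sample size of 207 participants (138 intervention, 69 control"; "Participants will be randomized in a 2:1 allocation ratio"; "to detect a medium effect size (Cohen’s d = 0.5"; "with α = 0.05, power = 0.80, and accounting for 30% attrition". From Limitations: 10 x 180 = 1800 minutes (30 hours) against 5 x 90 = 450 minutes (7.5 hours), a ratio of 4. From Statistical analysis plan: the model above and an adherence threshold of 80% of assigned sessions. Attendance, outside care and their link to prognosis are not in the document; the values used below are assumptions.

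**The plan's own figure.** Two-sided alpha 0.05 (sidedness assumed), power 0.80, d = 0.5 and 2:1 allocation need 48 + 96 = 144 completers (noncentral-t power 0.802). Dividing by 0.70 gives 48/0.7 = 68.6, so 69, and 96/0.7 = 137.1, so 138. The total is 207, which reproduces and is not in dispute.

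**Step 1: the model as written.** For participant i at visit t, with arm G and total minutes C:

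y_it = a + b_t + g·G_i + d_t·G_i + k·C_i + u_i + e_it

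Subtract baseline (b_0 = d_0 = 0):

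y_it − y_i0 = b_t + d_t·G_i + (e_it − e_i0)

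The term k·C_i cancels, and so would any G_i·C_i term. With complete data the estimate of d_t is the between-arm difference in mean change, and its SE is σ_e·√[2(1/138 + 1/69)]. Neither involves C. The same holds within each imputed data set.

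Numerical check on one simulated data set (207 participants, 4 visits, complete), with the whole treatment effect generated through contact minutes:

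| Fixed effects | T1 time x group (SE) | Group coefficient |
|---|---|---|
| time, group, time x group | −0.48389 (0.151) | −0.162 |
| + contact | −0.48389 (0.151) | 0.151 |
| + contact, group x contact | −0.48389 (0.151) | 0.280 |
| + contact, contact x time | 0.091 (0.226) | −0.227 |

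The second and third models report the same interaction although contact accounts for everything. T2 and T3 are likewise unchanged (−0.21861 and −0.31758). A separate simulation on another outcome scale gave −5.2011 (SE 1.613) under all of the first three models. With about 30% dropout and no imputation, the shift was at most 0.003.

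The group coefficient does move, by 0.151 − (−0.162) = 0.313 in the second model. That shifts the adjusted difference equally at every visit, including baseline, before any study contact has taken place.

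**Step 2: overlap of the arms.** At 80% adherence or more, in-study minutes are 8 x 180 = 1440 to 1800, against 4 x 90 = 360 to 450. The gap is 1440 − 450 = 990 minutes. Three SE sessions (540 minutes) already exceed full attendance in the control arm (450 minutes). Overlap must come from SE participants who stop early or from care outside the study.

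**Step 3: precision of a form that acts.** VIF = 1/(1 − r²), where r is the correlation of arm with minutes; the SE is multiplied by √VIF.

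| Assumed scenario | VIF |
|---|---|
| All at 80% adherence or more, no outside care | about 23 |
| The same, 30% with outside care averaging 300 minutes | about 6.8 |
| 30% early dropout, 85% attendance otherwise | about 2.7 |
| The same plus outside care | 1.6 to 2.3 |

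Power at d = 0.5 with all 207: SE = √(1/138 + 1/69) = 0.147 and 0.5/0.147 = 3.39, so power is about 92%. At VIF 6.8, 3.39/2.61 = 1.30 and power is about 25%. At VIF 2.1, 3.39/1.45 = 2.34 and power is about 65%. On the 144 planned completers, normal-approximation power is 80.7%, and an SE multiplied by 1.5 brings it to about 47%.

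**Step 4: bias of a form that acts.** In 2,000 simulated trials the true effect was −0.5 and contact had no causal effect. Attendance averaged roughly 85%, and in two of the three settings depended on a latent tendency to improve (log-odds slope 1.0 per SD).

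| Attendance | Unadjusted mean | Contact-adjusted mean |
|---|---|---|
| Unrelated to improvement | −0.50 | −0.48 |
| Better responders attend more | −0.50 | +0.80 |
| Better responders attend less | −0.50 | −1.81 |

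**The case against.** The covariate belongs to secondary analyses and the dose-response models are called exploratory, so the primary intention-to-treat test does not depend on them. This stands and limits the severity.

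The Limitations section is also candid. It describes usual care as a pragmatic rather than dose-matched comparator and accepts limited comparability of dose. A reader might infer that the authors are bound to claim an effect independent of contact time; the protocol nowhere says so. What remains is the explicit promise of a robustness check, which the stated model cannot deliver.

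A condensed article may leave the covariate's functional form to a fuller plan. That is fair, but the forms that change the interaction meet Steps 2 to 4. Equally, an analyst who reports adjusted differences at each visit would see the covariate act, so it would be too strong to say that every result must look robust. Those differences are not the stated test, and the adjustment behind them is still for a post-randomisation variable.

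A reader might also infer that any workable form is hopelessly collinear. The document does not support that: it permits ongoing counselling and counts outside minutes, and with heavy dropout plus outside care the VIF can fall below 2. The overlap then comes mainly from self-selected participants, so the causal question is still unanswered.

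**Conclusion.** The concern holds in this form. For the model as written, with complete or imputed data, the identity is algebraic and needs no assumption about attendance: the time x group estimates and SEs are the same with and without total contact minutes, and with group x contact. The promised check therefore cannot detect what it is meant to detect.

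For forms that act, minutes are post-randomisation in every scenario and strongly determined by arm. The size of the damage is assumption-dependent: VIF about 2 to 7 in plausible scenarios, above 20 among adherent participants without outside care, and below 2 with heavy dropout and outside care. The direction of bias depends on who attends, so no single power or bias figure should be quoted as the consequence.

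This should be fixed, but it does not threaten the trial. The primary test, the randomisation and the 207 are untouched.

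**What to change.** 1. Remove total contact minutes as a covariate offered to show robustness, and remove the sentences in Statistical analysis plan and Limitations that promise such a check.
2. Report in-study and outside-study minutes by arm descriptively.
3. State that the trial compares a 30-hour SE package with 7.5 hours of usual care and cannot separate SE content from contact time.
4. The exploratory dose-response models need not be deleted. Any contact-time model that is kept should be labelled exploratory, associational and non-causal, with its functional form in time stated and no robustness conclusion drawn from it.

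The cost is text edits only, with no change to sample size, randomisation or data collection. The price is a narrower claim: an effect of the package, not of SE content at equal contact.

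### Missing outcomes are to be imputed by regression or predictive mean matching with no mention of multiple imputation or pooling; applied once, this either inflates type I error or shrinks the effect

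*Protocol article*

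**What the plan says.** All references are to the protocol article.

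- **Statistical analysis plan, missing data:** "Missing data will be handled using regression imputation under the assumption that data are missing at random (MAR". The next sentence narrows this: "Specifically, predictive mean matching will be used to impute missing continuous outcome variables". The article calls the method suitable for longitudinal trial data.
- **Statistical analysis plan, model:** "The models will include fixed effects for time, group, and time x group interaction, and random intercepts for participants". The four visits are baseline, Week 10, Week 14 and Week 22 (T0 to T3).
- **Statistical analysis plan, analysis set:** "All analyses will follow the intention-to-treat (ITT) principle, including all randomized participants".
- **Sample size:** 207 participants (138 and 69) for d = 0.5, "with α = 0.05, power = 0.80, and accounting for 30% attrition".

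The article gives no number of imputations, no pooling rule and no list of imputation-model variables. It also does not say that only one completed data set will be analysed.

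**The concern.** Regression imputation, without further qualification, normally means filling each gap once and analysing the completed file as if every value had been measured. The mixed model would then compute standard errors for 207 complete participants, although the trial expects outcomes from only about 70% of them. The uncertainty about the filled-in values would appear nowhere.

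The primary claim is at stake. Standard errors that are too small produce false positives on PCL-5. An imputation model that ignores arm pulls the groups together and hides a real effect.

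The step is also avoidable. A likelihood-based mixed model on the observed values rests on the same missing-at-random assumption and needs no imputation, provided its covariance structure is adequate.

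**Working it through.** **1. The plan's own figure.** With d = 0.5, two-sided α = 0.05 (the article does not state sidedness), power 0.80 and 2:1 allocation, the two-sample t calculation gives 48 + 96 = 144. Allowing for 30% loss: 48/0.7 = 68.6, so 69; 96/0.7 = 137.1, so 138; total 207. The stated size reproduces, so 30% is the trial's own allowance for loss.

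**2. Hand check of the mechanism.** Assume unit variance and within-person correlation 0.5. The variance of a change score is then 2(1 − 0.5) = 1.

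- Standard error (SE) of the group difference in change with 207 complete: √(1/138 + 1/69) = 0.147.
- SE with 70% observed (96.6 and 48.3): √(1/96.6 + 1/48.3) = 0.176.
- An analysis that reports 0.147 when the true SE is 0.176 uses an effective critical value of 1.96 × 0.147/0.176 = 1.64. Its two-sided error is about 0.10.
- A single random donor draw adds noise. The simulated SE was 0.181 against a reported 0.147, so 1.96 × 0.147/0.181 = 1.59, an error of about 0.11.

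**3. Simulation under no effect.** Inputs from the article: 138/69, four visits, random-intercept model, 30% missing at T3. Assumed: correlation 0.3, 0.5 or 0.7; loss either graded (10/20/30% at T1/T2/T3) or 30% from T1 onward; completely random loss, plus one case depending on observed data. There were 3,000–4,000 trials per setting, so the Monte Carlo standard error near 5% is √(0.05 × 0.95/3,000) = 0.004.

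| Method (nominal 0.05) | T3 × group contrast | Joint time × group test |
|---|---|---|
| Deterministic regression, once, arm included | 0.111–0.138 | 0.151–0.261 |
| Stochastic regression, once, arm included | 0.099–0.124 | 0.13–0.22 (with PMM) |
| Predictive mean matching (PMM), once, arm included | 0.095–0.134 | 0.13–0.22 (with stochastic) |
| PMM, 20 imputations, pooled | 0.042–0.055 | not run |
| Mixed model, observed data only | 0.042–0.053 | 0.045–0.051 |

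**4. Dependence on attrition** (correlation 0.5, graded loss; deterministic regression or single PMM with arm). The T3 contrast error is 0.066–0.067 at 10% final loss and 0.087–0.094 at 20%.

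**5. Effect of the Bonferroni correction.** The article does not give the number of tests. If it is three (α = 0.0167), the single-imputation error at 30% loss and correlation 0.5 is 0.045–0.072 for the contrast and 0.068–0.132 for the joint test. The correction does not restore its intended level.

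**6. Arm left out of the imputation model.** Single PMM then keeps type I error at 0.040–0.058. However, imputed participants carry little or no arm difference. With 30% lost from T1 onward, the expected effect is 0.7 × 0.5 + 0.3 × 0 = 0.35; the simulation gave 0.345. With graded loss it gave 0.395, because earlier observed visits carry part of the effect. Power for the T3 contrast was 0.64 and 0.76, against 0.92 with complete data. On observed change scores alone it would be about Φ(0.5/0.176 − 1.96) = 0.81.

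**The case against.** The strongest reply is that single imputation is inferred from silence. Predictive mean matching can be run as multiple imputation, this is a condensed article, and the number of imputations and the pooling rule are often left to a separate analysis plan. When pooled, the method holds its level. **This stands**, and it is why every error rate here is conditional. It does not remove the point: the article names a method, endorses it, and sends the result into a model that needs no imputation under the same assumption.

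Second, the inflation requires arm in the imputation model, which the article does not state. **This also stands.** The alternative is not harmless, though, because it trades false positives for attenuation and lost power.

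Third, 30% is a planning allowance, and the article describes retention measures and keeps completed assessments from those who discontinue. **This stands in part.** With loss of 15/23/30% at the three visits, a separate simulation put the Week 10 contrast at only 8%. The larger joint-test figures matter only if the decision rests on that test, and the article does not say that it does.

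A reader might also infer that regression imputation and predictive mean matching contradict each other. The text does not support that: predictive mean matching uses a regression to choose donors, and the second sentence reads as a specification of the first.

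**Conclusion.** The concern holds conditionally. The article fixes an imputation step before the mixed model and leaves out what would make it valid. Run once at the planned 30% attrition:

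- with arm in the imputation model, type I error is about 10–14% for a visit-by-group contrast and 13–26% for the joint test, against a nominal 5%;
- without arm, the level holds, but a true d of 0.5 becomes about 0.35–0.40, with the power loss shown above.

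These sizes rest on assumed correlations and dropout patterns and on attrition near 30%.

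A reader might infer that the trial's type I error will at least double. The documents do not support that unconditional claim: they neither say that one data set will be used nor say what enters the imputation model, and attrition may be lower. What they do support is that the wording permits an invalid primary analysis and names neither of the two valid ones.

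**What to change.** Replace the imputation sentences with a statement that the primary analysis is the planned mixed model, fitted by REML to all observed PCL-5 values with no imputation. This is valid under missing at random if the covariance structure is adequate, so the random-intercept structure should be justified or made more flexible.

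If imputation is kept, state that it is multiple, that arm is in the imputation model, and that results are pooled by Rubin's rules. The number of imputations and the other predictors can be left to the analysts.

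The cost is a change of wording. Dropping imputation from the primary analysis reduces the work. The article schedules recruitment for January to June 2026 and completion of analysis for 2028, so the change can be made before outcomes are analysed.
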